#### Days Alive Outside Hospital (Olanzapine and Early Wakeup Interventions)

3.2.2

Days alive outside the hospital within 30 days will be analyzed using the Wilcoxon rank‐sum test between the two treatment arms. Results will be presented as medians with interquartile ranges and 95% confidence intervals for the median difference (calculated using non‐parametric bootstrapping with 1000 resamples). Relative differences between days alive outside hospital groups will be reported as percentages, with confidence intervals obtained by bootstrapping. As a prespecified supplementary analysis, days alive outside the hospital within 30 days will also be expressed as the mean between‐group difference with a 95% confidence interval. Sensitivity analyses using mixed‐effects linear regression models with site as a random effect, adjusting for other interventions, will be performed to assess the robustness of the findings.

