#### Primary Outcomes

2.5.1

The trial employs intervention‐specific primary outcomes:
Dexamethasone intervention: All‐cause mortality at 90 days.Backrest elevation intervention: All‐cause mortality at 90 days.Olanzapine intervention: Days alive outside hospital within 30 days.Early wakeup intervention: Days alive outside the hospital within 30 days.

The choice of intervention‐specific primary outcomes reflects the anticipated mechanism of action for each intervention. Dexamethasone and backrest elevation target pathophysiological pathways that may directly affect early survival—dampening systemic inflammation and increasing cerebral perfusion pressure, respectively—thereby making 90‐day all‐cause mortality the most clinically relevant primary endpoint. In contrast, olanzapine and the early wakeup strategy primarily aim to reduce delirium and sedation‐related complications, translating into improved functional recovery and shorter hospital stays rather than a direct effect on mortality. Days alive outside the hospital within 30 days reflect both survival and time to recovery, and are therefore a more sensitive and clinically meaningful primary endpoint for these two interventions.

Days alive outside the hospital within 30 days are calculated by subtracting the time spent in the hospital or deceased within 30 days, then rounding down to the nearest whole number. Thus, a patient dying on admission day has zero days alive outside the hospital, and a patient with hospitalization exceeding 30 days also has zero days alive outside the hospital. A day (≥ 24 h) spent at a hospital or healthcare facility operated by a Danish region counts as time in hospital, whereas outpatient visits and brief hospitalizations < 24 h count as days alive outside hospital.

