### Sample Size

2.6

The trial aims to include 1000 patients across five sites, covering the entire Danish population. Sample size calculations were performed separately for each intervention based on its primary outcome.

For the Dexamethasone and backrest elevation interventions (primary outcome: 90‐day mortality), assuming an overall mortality of 35% and a 25% relative risk reduction (to 26% mortality), with 85% power and a two‐sided significance level of 5%, 468 patients per group are required. To account for potential dropouts and loss to follow‐up, 500 patients per group (1000 total) are planned.

For the olanzapine and early wakeup interventions (primary outcome: days alive outside hospital within 30 days), estimates assumed 35% mortality during initial hospitalization (0 days alive outside hospital) and a mean of 15 days outside hospital for survivors, yielding a population mean of 9.8 days with an estimated standard deviation of 7 days. To detect an increase of 1.5 hospital‐free days with > 90% power and a two‐sided significance level of 5%, a total of 920 patients were required.

The combined sample size of 1000 patients provides adequate power for all four primary outcomes within the factorial design. The trial is not powered to detect interactions between interventions; prespecified interaction analyses (Section 3.5) are exploratory and hypothesis‐generating.

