#### Count Data

3.3.3

Count data (intensive care unit length of stay, hospital length of stay, duration of intubation, days without delirium treatment) will be analyzed using the Wilcoxon rank‐sum test. Results will be presented as medians with interquartile ranges and 95% confidence intervals for the median difference obtained by bootstrapping.

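### For olanzapine and early wakeup, the bootstrapped median-difference interval set beside the Wilcoxon test matches neither that test nor the sizing, and would often disagree with the test if a true effect near the design size exists

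*SAP article*

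**What the plan says.** Section 2.5.1 makes days alive outside hospital within 30 days the primary outcome for olanzapine and for early wakeup. The value is obtained by subtracting time in hospital or dead, "then rounding down to the nearest whole number". A death on the admission day or a stay beyond 30 days scores zero.

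Section 3.2.2 fixes the analysis: "Days alive outside the hospital within 30 days will be analyzed using the Wilcoxon rank"-sum test. For presentation it states "Results will be presented as medians with interquartile ranges and 95% confidence intervals for the median difference", from "bootstrapping with 1000 resamples". It adds, as a supplementary analysis, that the outcome "will also be expressed as the mean between"-group difference with a 95% CI. Mixed-effects linear regression is a sensitivity analysis.

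Section 2.6 assumes 35% in-hospital mortality at zero days and a survivor mean of 15 days, "yielding a population mean of 9.8 days with an estimated standard deviation of 7 days". It sizes for a gain of 1.5 days.

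Nothing in the article says which result governs the reading if the Wilcoxon p-value and the median interval disagree.

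**The concern.** Three different quantities serve one primary outcome: the test compares whole distributions, the interval beside it concerns medians, and the sizing concerns means.

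Wilcoxon speaks about medians only if one distribution is the other moved sideways. Deaths stay at zero in both arms, so that cannot hold here. With 35% at zero, the overall median reflects only survivors with long stays.

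For two of the four interventions, the report could show a significant test beside an effect interval that includes zero. That interval could not be set against the planned 1.5 days. Because the mean interval is also prespecified, the choice of which result to stress would be left open until results are known.

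**Working it through.** **1. Reproduce the sizing.** Inputs from Section 2.6: difference 1.5, SD 7, power 90%, two-sided 5%.

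n per arm = 2 × (1.960 + 1.282)² × 7² / 1.5² ≈ 458, or 916 in total against the stated 920. Power is 90.1% at 460 per arm and 92.3% at 500 per arm. The stated figure is a difference-in-means calculation.

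**2. Where the median falls.** The mean is 0.65 × 15 = 9.75, the plan's 9.8. The overall median lies at (0.50 − 0.35) / 0.65 = 0.23, the 23rd percentile of survivors. Stays beyond 30 days also score zero, so the share at zero can exceed 35%, which moves the median further down.

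**3. How often test and interval disagree.** Inputs from the plan: 35% zeros, survivor mean 15, 500 per arm, whole days, 1000 resamples.

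Assumptions:
- Survivor SD is not given. It was taken as 5 or 7, with a beta shape on 0-30 days.
- The bootstrap interval is the percentile type.

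There were 1500 simulated trials per scenario. Disagreement means that exactly one of the following is true: Wilcoxon p < 0.05, or the 95% CI excludes 0. Cells give SD 5 / SD 7.

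| Scenario | Wilcoxon p < 0.05 | Median CI excludes 0 | Disagree: median CI | Disagree: mean CI |
|---|---|---|---|---|
| No effect | 4.8 / 4.7% | 1.3 / 1.6% | 4.0 / 3.4% | 0.8 / 0.7% |
| Stay only: survivors 15 to 17.3 days (mean gain 1.5) | 86 / 62% | 56 / 36% | 30 / 26% | 7.5 / 9.7% |
| Mortality only: 35% to 25% (mean gain 1.5) | 80 / 81% | 31 / 43% | 49 / 37% | 5.1 / 3.4% |
| Mixed: 35% to 31%, 15 to 16.4 days | 86 / 73% | 53 / 47% | 33 / 27% | 3.9 / 3.5% |
| Stay only, mean gain 1.0 | 53 / 30% | 23 / 14% | 31 / 18% | 8.1 / 7.7% |

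The gains follow from 0.65 × 2.31 = 1.5 and 0.75 × 15 − 0.65 × 15 = 1.5. Nearly all disagreement runs one way. In the stay-only case with SD 5, 29.9 of the 30.1 percentage points are p < 0.05 with a CI that includes 0.

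**4. Other survivor shapes and interval types.** Runs with normal survivors (SD 4 to 8) or skewed shapes, near the design effect, gave:
- percentile median CI: 21-48% disagreement; in one further run (SD 4, mortality only) it reached 56%
- normal-based median CI: 11-41%
- mean CI: 3-11%
- Mann-Whitney probability CI: 0%

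**5. Width and coverage.** The median interval was 2.8-7.9 days wide, against 2.0-2.5 for the mean, about 1.4 to 3 times as wide. With no effect it covered 97-99%, and the mean interval about 95%.

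**6. If zeros reach about half (assumption).** Both medians become 0. The median CI excluded 0 in 0-2% of trials while Wilcoxon rejected in 32-60%.

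**The case against.** The same section already prespecifies the mean difference with a 95% CI, so the sizing quantity will be reported. The plan never calls the median difference its primary effect. The test makes the significance decision, and its type I error is untouched. All of that stands. What remains is that the only absolute effect measure attached to the primary test does not correspond to it.

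The rates depend on choices the plan does not fix. It does not name the type of bootstrap interval, and a normal-based one lowers the disagreement. Many percentile intervals counted as including 0 had a limit exactly at 0 (97% of them at SD 4, 89% at SD 6). The simulated population SDs exceed the plan's 7, but 35% zeros and a survivor mean of 15 already force at least 15 × √(0.35 × 0.65) = 7.15, so no scenario with these inputs can match 7.

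The mean does not match Wilcoxon exactly either. In one smaller set of runs at survivor SD 4, the mean CI disagreed with the test in 20% of trials, against 24% for the percentile median CI and 12% for the normal-based one. This stands, and it is why the rank-based estimate should accompany the p-value.

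A reader might infer that conflict is likely whatever the truth. The runs without an effect do not support that, and Section 3.1 itself notes that almost all earlier hospital-phase trials were neutral. A reader might also carry the argument to the count outcomes in Section 3.3.3 or to the transformations in Section 3.7.1.1. Nothing was shown for length of stay or intubation time, and transformations are only to be considered if model assumptions fail.

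**Conclusion.** The concern holds in a limited form. The median-difference interval in Section 3.2.2 is neither what the Wilcoxon test assesses nor what the trial was sized on. Both follow from the plan's own inputs.

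Given a true effect near the design size, test and interval would disagree in roughly 20-50% of trials with a percentile bootstrap, and in roughly 10-40% with a normal-based one. This assumes survivor SD 4-8 or a skewed shape, 35% zeros and 500 per arm. Without an effect the figure is about 3-4%.

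The documents do not support reading this as an invalid primary test or as an interval biased towards benefit: the interval errs on the conservative side. This is a reporting choice worth correcting before results are seen.

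**What to change.** In Section 3.2.2:
- Report the Mann-Whitney probability (the chance of more days on intervention than on control, plus half the ties) with its 95% CI, as the estimate that belongs to the Wilcoxon p-value.
- Move the prespecified mean difference in days with its 95% CI from supplementary analysis to main effect size in days, so that it can be set against the planned 1.5 days.
- Keep medians with quartiles as description, and do not use the median-difference CI for inference.

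Leave Sections 3.3.3 and 3.7.1.1 as they are.

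The cost is SAP wording. The mean interval is already planned and the rank-based estimate uses the same data. The downside is that readers may be less used to a probability or a mean for a skewed outcome, which keeping the medians in the table eases.

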### Analysis of Secondary Outcomes

3.3

#### Dichotomous Outcomes

3.3.1

No secondary or tertiary endpoints are adjudicated by a blinded endpoint committee. Dichotomous outcomes (mortality at other time points, unconsciousness at 96 h, and Confusion Assessment Method for the Intensive Care Unit positivity) will be analyzed using the chi‐square or Fisher's exact test, as appropriate. Results will be presented as proportions with risk ratios and 95% confidence intervals. Mixed‐effects logistic regression models with site as a random effect and other interventions as fixed effects will be used for adjusted analyses.

#### Continuous Outcomes

3.3.2

Continuous endpoints assessed at multiple time points will be analyzed using linear mixed models, including a random intercept for each patient and a random effect for site. The treatment‐by‐time interaction will indicate whether the endpoint changes differently over time in the intervention versus control groups. Group differences will be reported as relative percentage differences. A logarithmic transformation will be applied to approximate a normal distribution as appropriate. Non‐parametric bootstrapping with 1000 resamples will be applied in case of deviations from distributional assumptions.

Continuous outcomes measured at a single time point will be analyzed using mixed‐effects linear regression with site as a random effect and other interventions as fixed effects. Results will be presented as mean differences with 95% confidence intervals.

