### Randomization and Blinding

2.3

Randomization is performed in a 1:1 factorial design for all four interventions, using sealed intervention boxes containing study drugs and written instructions. Randomization is generated with varying block sizes to ensure balance across the 16 possible intervention combinations. The balance of allocation across the 16 possible combinations is monitored when generating the randomization sequence and as part of the planned interim analyses.

Pharmacologic interventions (dexamethasone and olanzapine) are double‐blinded, with study drugs prepared by the pharmacy in the Capital Region of Denmark and administered by nurses uninvolved in the patient's care. Physiologic interventions (backrest elevation and early wakeup) are open‐label because blinding them is inherently difficult. Outcome assessors, statisticians, data managers, the steering group, and the data safety and monitoring committee will be blinded to treatment allocation.

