### General Principles

3.1

All analyses will be conducted according to the modified intention‐to‐treat principle, including all randomized participants who meet the inclusion criteria and have available outcome data, or imputed outcome data (see missing data section below). Participants who do not fulfill the inclusion criteria will be excluded from analyses. If consent is subsequently withdrawn, data collected prior to withdrawal will be included in the primary analysis in accordance with the EU Clinical Trials Regulations, unless the participant explicitly requests deletion of their data. A per‐protocol analysis will be performed as a sensitivity analysis, including only participants who received all scheduled doses of pharmacologic interventions, adhered to the assigned backrest position for ≥ 80% of the time, and had a wakeup call attempted within the assigned time frames.

Data will be analyzed and reported as four individual trials, with no adjustment for multiple comparisons planned. This approach is justified because almost all previous trials in the hospital phase of out‐of‐hospital cardiac arrest care have been neutral, and all four interventions are accepted without considering potential interactions. If more than one intervention shows a non‐neutral result, interactions between interventions will be evaluated by including pairwise and higher‐order interaction terms in the primary regression models for each intervention, applying the prespecified thresholds defined in Section 3.5 (interaction *p* < 0.01 and absolute effect ≥ 5.6%). If a clinically important interaction is identified, results for the affected interventions will be presented both as overall estimates and stratified by the interacting intervention allocation. All regression analyses will be adjusted for site as a covariate.

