#### Ordinal Outcomes

3.3.4

Cerebral Performance Category and modified Rankin Scale at discharge and follow‐up will be analyzed as ordinal outcomes using proportional odds models with robust standard errors clustered by site and other interventions as fixed effects. Results will be reported as odds ratios with 95% confidence intervals. Proportional odds assumptions will be assessed using Brant tests.

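### The repeated-measures model in section 3.3.2 does not name the other three randomised allocations, so intervals for the exploratory markers may be modestly too wide

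*SAP article*

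**What the plan says.** Section 3.3.2 describes the model for repeatedly measured continuous endpoints as "including a random intercept for each patient and a random effect for site". It adds that the treatment-by-time "interaction will indicate whether the endpoint changes differently over time in the intervention versus control groups". No other fixed effects are named.

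The neighbouring regression models are more explicit:

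- Single-time continuous outcomes, in the next paragraph of 3.3.2: mixed-effects "linear regression with site as a random effect and other interventions as fixed effects".
- Adjusted dichotomous analyses, 3.3.1: mixed-effects "logistic regression models with site as a random effect and other interventions as fixed effects will be used for adjusted analyses".
- Ordinal outcomes, 3.3.4: proportional odds models with "robust standard errors clustered by site and other interventions as fixed effects".

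The sensitivity model for days alive outside hospital in 3.2.2 also adjusts for the other interventions. The one rule in 3.1 that covers every regression supplies site only: "All regression analyses will be adjusted for site as a covariate". Section 2.3 says that varying block sizes are used to "ensure balance across the 16 possible intervention combinations".

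The common endpoints this model serves are listed as exploratory (tertiary) in 2.5.3: inflammatory and organ markers over the first 72 h, and neurofilament light chain and neuron-specific enolase at 0, 24, 48 and 72 h.

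**The concern.** An analyst who follows 3.3.2 as written would fit one allocation, time, a patient intercept and a site effect, and leave the other three allocations out. This is the class of endpoint where one randomised factor is most likely to have a real effect, because the Background gives inflammation as the target of dexamethasone. An effect that grows between baseline and 72 h is a systematic, known difference between patients. A model for olanzapine, backrest or wakeup that lacks it treats it as noise.

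At stake is precision on the mechanism markers of the interventions other than the one that moves the marker. Their intervals would be wider than the design warrants, and some true effects would be missed although the data could show them.

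**Working it through.** The SAP states no standard error, power or interval width for this model, so there is no figure of its own to reproduce.

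**Inputs.** From the SAP: 1:1 allocation for each factor with blocks over 16 cells (2.3), about 1000 patients (2.6), sampling at 0, 24, 48 and 72 h (2.5.3), and treatment-by-time as the term to interpret (3.3.2). Assumed: time is categorical; the omitted allocation shifts the marker by d marginal SDs at 24, 48 and 72 h and not at 0 h; the within-patient correlation ρ is 0.3, 0.5 or 0.7. The simulations use 1008 patients, 63 in each of 16 cells.

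**Formula.** Code the omitted allocation as ±1/2 and set the marginal variance to 1. The true within-patient variance is 1 − ρ. The omitted effect pattern is d × (0, 1, 1, 1), with mean 0.75d. Its squared deviations sum to (0.75² + 3 × 0.25²)d² = 0.75d². Multiplying by (1/2)² and dividing by the 3 within-patient degrees of freedom gives d²/16. The reported SE of another intervention's 72 h versus 0 h contrast, relative to the correct one, is therefore

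ratio = √(1 + d² / [16(1 − ρ)]).

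| d (SD) | ρ = 0.3 | ρ = 0.5 | ρ = 0.7 |
|---|---|---|---|
| 0.2 | 1.002 | 1.003 | 1.004 |
| 0.5 | 1.011 | 1.016 | 1.026 |
| 1.0 | 1.044 | 1.061 | 1.099 |
| 1.5 | 1.096 | 1.132 | 1.212 |

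For example, d = 1 and ρ = 0.7 gives √(1 + 1/4.8) = 1.099. On a log scale, a marker halved by dexamethasone with an assumed log SD of 1 has d = ln 2 = 0.69, so d² = 0.48. The ratio is then √(1 + 0.48/11.2) = 1.02 at ρ = 0.3 and √(1 + 0.48/4.8) = 1.05 at ρ = 0.7.

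**Simulation (1500 runs per setting).** The ratios agree with the table. At d = 1, ρ = 0.7 the true SD of the estimate was 0.0485 with or without the omitted terms. The mean reported SE was 0.0536 without them and 0.0488 with them, and coverage of the nominal 95% interval was 97.6% and 95.8%. At d = 1.5, ρ = 0.7 coverage was 98.3% and 95.3%. The Monte Carlo error of a coverage figure is about √(0.95 × 0.05/1500) = 0.6 percentage points.

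**Which terms matter.** One simulated data set at d = 1, ρ = 0.5 was fitted with a random-intercept mixed model. The SE of the other intervention's 72 h interaction term was 0.0685 without the other allocations, 0.0685 with them as main effects only, and 0.0644 with their time interactions as well. The ratio is 0.0685/0.0644 = 1.064. Main effects alone gain nothing for this term.

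**Dependence on balance.** With independent allocation instead of balanced cells (d = 1, ρ = 0.5), the estimate's SD was 0.0705 without the terms and 0.0628 with them, and coverage was 94.1% and 95.3%. The finding that the error is conservative therefore rests on the blocked allocation. Adjustment helps in either case.

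**The case against.** The strongest objection is that the quoted phrase lists random effects only. It does not name even treatment or time as fixed effects; these emerge from the following sentence. Its opening word need not introduce a complete list, so a reader might infer a deliberate exclusion that the text does not show. This stands as a caution. Silence is still worth repairing, because three neighbouring models name the term and nothing elsewhere supplies it.

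Second, leaving out co-allocations is common in this plan. The log-binomial primary model, the rank-sum tests and the chi-square tests name none, and 3.1 treats the data as four separate trials. Analysis at the margins of a balanced factorial is valid. That also stands: the point concerns efficiency and consistency with the adjacent regression models, not validity.

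Third, a reader might infer a larger loss from the formula for a single sampling time, √(1 + d²/4), which gives 1.118 at 1 SD and 1.250 at 1.5 SD. That is a different analysis. The term the plan says it will interpret is treatment-by-time, and its inflation is smaller over the correlations examined.

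Fourth, a reader might infer that the plan handles one marker in two ways, depending on whether it is measured once or repeatedly. No instance appears: every marker in 2.5.3 is serial or described over a 72 h window. Nor do the documents predict how far any intervention moves any marker, including the two brain-injury markers.

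**Conclusion.** The point holds as a minor one. Section 3.3.2 leaves out of its description terms that the adjacent models include. Where another intervention really moves a marker, the reported treatment-by-time intervals come out modestly too wide: negligibly for a 0.2 SD effect, by a few per cent for effects around half an SD, and by 10% or more only for effects well above 1 SD or for about 1 SD with high within-patient correlation. Markers that no other intervention moves are unaffected.

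These sizes rest on assumed effects and correlations, a step effect after baseline, and close balance over the 16 cells. Under that balance there is no bias and no type I error inflation, so a reader should not infer that the marker results would be misleadingly positive. The listed endpoints are exploratory and no primary conclusion depends on them.

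**What to change.** In 3.3.2, state that the repeated-measures model includes all four allocations and their interactions with time as fixed effects, and that each intervention's effect is read from its own allocation-by-time terms. Copying the wording of the next paragraph would not be enough, because it gives main effects only.

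The cost is one sentence. With four categorical sampling times it adds 3 main effects and 3 × 3 = 9 interaction terms, 12 fixed effects per marker, which is small against about 1000 patients. No new data are needed.

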#### Exploratory (Tertiary) Outcomes

2.5.3

All‐cause mortality at 180 days and 1 year.Inflammatory and organ markers during the initial 72 h.Neurofilament light chain and neuron‐specific enolase at 0, 24, 48, and 72 h.Cognitive function assessment (Repeatable Battery for the Assessment of Neuropsychological Status, Trail Making Test, and Montreal Cognitive Assessment) at 3–6 months.

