All statistical significance tests will be two‐sided, with a significance level of 5%. No alpha spending or adjustment of the final significance level is required, as the planned interim analysis at 500 enrolled patients is a safety review conducted by the independent data‐monitoring committee without formal efficacy or futility testing (see Section 3.9). Throughout, categorical variables will be presented as counts with proportions, whereas continuous variables will be presented as means ± standard deviations for normally distributed variables or medians (25th–75th percentiles) for nonnormally distributed variables. The normal distribution will be evaluated using quantile‐quantile plots.

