##### Mixed‐Effects Models

3.7.1.1

For mixed‐effects logistic and linear regression models, the following assumptions will be assessed:
Normality of residuals (linear models): Assessed using quantile‐quantile plots of residuals.Homogeneity of variances (linear models): Assessed by plotting residuals against covariates and fitted values.Random effects structure: Appropriateness of site as a random effect will be assessed using likelihood ratio tests. Normality of random effect estimates will be assessed using quantile‐quantile plots.

If assumptions are violated, appropriate transformations (logarithmic, square root), robust standard errors, or bootstrapping will be considered.

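### As written, the repeated-marker model in section 3.3.2 assumes equal correlation across 0 to 72 h and no listed check tests this; 72 h standard errors can be miscalibrated for exploratory markers (minor)

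*SAP article*

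**What the plan says.** Section 3.3.2 (Continuous Outcomes) sets the model for endpoints measured at several times: a linear mixed model "including a random intercept for each patient and a random effect for site". The term to be interpreted is treatment by time: the "interaction will indicate whether the endpoint changes differently over time in the intervention versus control groups". The section does not say whether time is categorical or linear, and it names neither a random slope nor a residual covariance. Its fallback is that "bootstrapping with 1000 resamples will be applied in case of deviations from distributional assumptions"; the resampling unit is not given.

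Section 2.5.3 lists neurofilament light chain and neuron-specific "enolase at 0, 24, 48, and 72 h", and "Inflammatory and organ markers during the initial 72 h", all as exploratory (tertiary) outcomes.

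Section 3.7.1.1 lists the mixed-model checks. The first is "Normality of residuals (linear models): Assessed using" quantile-quantile plots. The others are homogeneity of variances, from plots of residuals against covariates and fitted values, and the site random effect. If an assumption fails, transformation, robust standard errors or bootstrapping are to be considered.

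**The concern.** A patient random intercept with independent residuals gives a compound-symmetric covariance: equal variance at each time and equal correlation for each pair of times. Markers that evolve over three days after an arrest may well be more alike at 24 h apart than at 72 h apart. The treatment-by-time term is built from within-patient changes, so its standard error depends directly on that assumption.

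The listed safeguards aim elsewhere. A marker that looks normal on the log scale, with stable variance but correlation that fades with lag, would pass every check in section 3.7.1.1. The bootstrap in section 3.3.2 would not be triggered either, because its trigger is distributional. At stake is the calibration of intervals and p-values for changes from baseline in the exploratory markers.

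**Working it through.** The SAP states no correlation, standard deviation or standard error for any repeated marker, so there is no figure of its own to reproduce. The check compares the variance that the model would report with the true variance under assumed covariances.

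**Inputs from the SAP**
- Four times: 0, 24, 48 and 72 h (section 2.5.3).
- Random intercept per patient, no residual structure named (section 3.3.2).
- Two-sided tests "with a significance level of 5"% (section 3.1).
- Size: "The trial aims to include 1000 patients across five sites" (section 2.6), allocated 1:1 for each intervention. Size cancels from the ratios below.

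**Assumptions**
- Complete data at all four times.
- AR(1) correlation between adjacent times of 0.5, 0.7 or 0.8, with unit variance. These values are not in the SAP.

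**Formulas**
- Let S be the true 4 × 4 covariance. With balanced data, the random-intercept model estimates the residual variance as s² = (mean variance) − (mean covariance). It gives every change between two times a variance proportional to 2s².
- The true variance of the change from time 0 to time j is proportional to S00 + Sjj − 2·S0j.
- SE ratio (model/true) = √[2s² / (S00 + Sjj − 2·S0j)].
- Actual type I error = 2·[1 − Φ(1.96 × ratio)].

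**Worked case, AR(1) = 0.7**
- The six covariances are 0.7 (three times), 0.49 (twice) and 0.343 (once). Their mean is (2.1 + 0.98 + 0.343)/6 = 0.5705.
- s² = 1 − 0.5705 = 0.4295, so 2s² = 0.859.
- 0 to 72 h: true value 2 − 2 × 0.343 = 1.314; ratio √(0.859/1.314) = 0.81; type I error 11.3%.
- 0 to 24 h: true value 2 − 2 × 0.7 = 0.60; ratio √(0.859/0.60) = 1.20; type I error 1.9%.

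**Range**

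| AR(1) | 2s² | True, 0 to 72 h | Ratio | Type I error | True, 0 to 24 h | Ratio | Type I error |
|---|---|---|---|---|---|---|---|
| 0.5 | 1.292 | 1.750 | 0.86 | 9.2% | 1.000 | 1.14 | 2.6% |
| 0.7 | 0.859 | 1.314 | 0.81 | 11.3% | 0.600 | 1.20 | 1.9% |
| 0.8 | 0.603 | 0.976 | 0.79 | 12.3% | 0.400 | 1.23 | 1.6% |

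The 72 h ratios of 0.86 to 0.79 mean standard errors 14 to 21% too small.

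**Simulation.** With 500 per arm and 4000 runs per setting, AR(1) of 0.5, 0.7 and 0.8 gave rejection rates of 9.6%, 11.9% and 12.0% for the 72 h contrast and 2.4%, 2.0% and 1.4% for the 24 h contrast. The joint 3-df interaction test rejected in 5.9%, 6.3% and 6.3%; with an unstructured covariance it rejected in 5.3%, 4.8% and 5.0%.

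**Other covariances**
- True compound symmetry: ratio 1.00, type I error 5.0% for every contrast.
- SDs rising then falling (0.6, 1.0, 1.2, 0.6) with equal correlation 0.6: 2s² = 0.74 against a true 0-to-72 h value of 0.288, so the ratio is 1.60 and the type I error 0.2%. The 72 h standard error is then too large.
- The same SDs with AR(1) 0.7: ratio 1.25, type I error 1.5%.
- Linear time under AR(1) 0.5 to 0.8: slope ratio 0.81 to 0.74, type I error about 11 to 15%. This applies only if time is entered linearly, which section 3.3.2 leaves open.

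**The case against.** A reader might infer that the plan makes 72 h standard errors too small outright. The documents do not support that. They give no covariance for any marker, and the working shows a correct standard error under compound symmetry and one that is too large when variance peaks mid-course.

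A reader might also infer that the random intercept is the only dependence allowed. Section 3.3.2 says the model includes it; another residual structure is unnamed rather than ruled out, and a journal article may leave model options to the full plan or code. This stands in part. But the article does state a within-patient structure and the term to be read from it, and an analyst following that text would fit the restrictive model.

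Third, the SAP speaks of the treatment-by-time interaction, not of a 0-to-72 h contrast. With categorical time the natural test is the joint one, and its inflation is about one percentage point. This stands, and the 9 to 12% must not be read as the error rate of that test. It applies to single-time contrasts if they are reported.

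Fourth, the residual plots in section 3.7.1.1 could reveal variance that changes over time, a log transformation might reduce it, and robust standard errors are already named as a remedy. That also stands for unequal variance. It does not cover correlation that decays at constant variance, which no listed check examines.

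Finally, the named markers are exploratory, so little rests on them. This sets the severity.

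**Conclusion.** The point holds in a limited form. Followed as written, section 3.3.2 imposes equal variance and equal correlation over 0 to 72 h, and section 3.7.1.1 has no check on within-patient correlation. If correlation decays with lag, late contrasts are anti-conservative and early ones conservative, by the amounts tabulated, while the joint test stays near its nominal level. All of this rests on assumed AR(1) values and complete data; the size and even the direction depend on a covariance that the SAP does not give. No primary outcome and no sample size calculation uses this model. Severity is minor, but the remedy is cheap enough to be worth making.

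**What to change.** In section 3.3.2, state that time is categorical and that the within-patient residual covariance is unstructured over the four times. That is 4 variances plus 6 covariances, or 10 parameters, which is easily supported by about 1000 planned patients. Add a fallback for non-convergence: the random-intercept model with robust standard errors clustered on patient, or a bootstrap that resamples whole patients. State that resampling unit for the bootstrap already planned there.

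The cost is a sentence or two in the SAP and a model option in the code, with slight extra computing. No further data are needed. The downside is possible non-convergence, which the fallback covers.
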